## Discussion

Untreated IPF has the worst prognosis among the different forms of ILD, with median survival ranging from 3 to 5 years from diagnosis [60]. Recent studies suggest that if novel anti-fibrotic medications (pirfenidone and nintedanib) are started early, they can slow the rate of lung function decline and prevent IPF exacerbation, thus reducing mortality [6, 7]. Unfortunately, because of the unspecific nature of the symptoms, the early stage of IPF remains underdiagnosed and many patients will progress to advanced disease and may require lung transplantation [8]. By contrast, the prognosis of NSIP is generally better than that of IPF, with a median survival time of more than 9 years. Systemic steroids and immunosuppressive therapy may be attempted to slow or reverse the course of the disease, but non-responsive individuals may also be considered for lung transplantation [8]. When left untreated, NSIP tends to progress toward fibrotic changes and persistent debilitating symptoms. COPD is also a leading cause of disability worldwide. Patients are generally unaware of their condition for years, leading to a significant delay in diagnosis, the application of preventive measures such as a smoking cessation intervention, and potential treatment [61]. Being able to recognise and diagnose these lung diseases earlier is of the utmost clinical importance.

This study will aim to collect a standardised dataset of digital lung auscultations and derive a deep leaning model able to detect the acoustic and sonographic signatures of the presence and severity of IPF, NSIP and COPD. Recent advances in deep learning are promising to support doctors in standardising the detection and interpretation of complex patterns in pulmonary diseases and AI has proven to outperform doctors in discriminating respiratory pathologies via respiratory functional explorations [62], symptoms [63, 64] and/or radiological examinations [34]. To overcome the subjectivity of human auscultation and the discrepancy in auscultation ability between doctors [16], the development of AI algorithms for the analysis of respiratory acoustic signals has been proposed [19, 20]. In order to meet this requirement, many attempts have been made to develop and apply neural networks to automate the detection and classification of various disease-related breath sounds using machine learning and deep learning-based analysis [14, 64–66]. In particular, recent literature reviews have summarized advances in the implementation of respiratory sound-based AI algorithms in the screening, diagnosis, and classification of COPD [26, 65]. Conversely, the current state of knowledge on the computerized analysis of breath sounds in patients with ILD using AI techniques has not been assessed. Table 2 summarizes the published studies most similar to our research.

**Table 2 Tab2:** Overview on computerized respiratory sound analysis in ILDs using AI techniques

Related works	Sample size	Purpose	Features	Performance	Issues
Aykanat et al. [67]	40 IPF, 211 COPD, and 574 other pulmonary single or mixed conditions, 805 healthy subjects	Binary classification (healthy vs pathological) and 12-class lung disease classification	SVM, k-NN, GB	Performance for binary classification: Acc 88% to 92% Se 85% to 92% Sp 85% to 88% Performance for lung disease classification: Acc 43% to 68% Se 53% to 96%	Severity classification not done. LUS not used
Charleston-Villalobos et al. [68]	19 ILD (12 IPF, 7 extrinsic allergic alveolitis), 8 healthy subjects	Binary classification (healthy subjects vs patients with ILD)	AR model, SNN	Performance evaluation of the neural network: Acc 76.9% to 98.8%, Se 80.4% to 100%, Sp 73.3% to 100%	Severity classification not done. LUS not used
Flietstra et al. [69]	39 IPF, 95 CHF, 123 PN	Binary classification (IPF vs CHF and IPF vs PN)	BPNN, SVM	Acoustic properties of fine crackles of IPF help distinguish them from crackles of CHF and PN	No healthy subjects. Severity classification not done. LUS not used
Fukumitsu et al. [70]	71 ILD (24 honeycombing + , 47 honeycombing-)	Predicting honeycombing on HRCT by the acoustic properties of fine crackles	FFT	Acoustic properties of fine crackles distinguish the honeycombing from the non-honeycombing group	No healthy subjects. Severity classification not done. LUS not used
Horimasu et al. [71]	34 ILD, 8 COPD or asthma, 7 lung tumor, 5 lung nodule, 6 other	Comparisons of machine-learning-based quantification of four types of lung sounds between lung fields with and without ILD in HRCT and chest X-ray	Described in [72]	AUROC 0.855, Acc 75%, Se 76.1%, Sp 73.6%	Severity classification not done. Results suffered from the presence of background noise. LUS not used
Kahya et al. [73]	23 ILD, 28 COPD, 18 healthy	Binary classification (healthy vs pathological)	AR model, k-NN	Acc 71.1%	Severity classification not done. LUS not used
Kim et al. [74]	112 ILD, 211 COPD, 497 other pulmonary conditions, 51 healthy	Binary classification (healthy vs pathological) and three-class (crackles vs wheezes vs rhonchi) classification	CNN	Performance for binary classification: AUROC 0.93 Acc 86.5% Performance for abnormal sounds classification: AUROC 0.92 Acc 85.7%	Severity classification not done. LUS not used
Malmberg et al. [75]	8 fibrosing alveolitis, 8 emphysema, 8 asthma, 8 healthy subjects	Diagnosis agreement between clinical and machine-learning-based classification of lung sounds	FFT, SOM	Kappa for fibrosing alveolitis 0.54	Small number of patients. Severity classification not done. LUS not used
Manfredi et al. [76]	98 CTD patients (42 ILD + , 56 ILD-)	Identifying CTD patients with possible ILD using lung sound-based binary classification (presence vs absence of ILD) compared with chest HRCT	FFT	Acc 82.6%, Se 88.1%, Sp 78.6%	No healthy subjects. Severity classification not done. LUS not used
Manfredi et al. [38]	137 RA patients (59 ILD + , 78 ILD-)	Identifying RA patients with possible ILD using lung sound-based binary classification (presence vs absence of ILD) compared with chest HRCT	FFT	Overall performance: Acc 83.9%, Se 93.2%, Sp 76.9% Performance for velcro-like crackles detection: Acc 67.2%, Se 69.1%, Sp 65.7%	No healthy subjects. Severity classification not done. LUS not used
Messner et al. [77]	7 IPF, 16 healthy subjects	Binary classification (healthy subjects vs patients with IPF)	CRNN	F-score 92.4% Se 85.9%	Small number of patients. Manual crackles labelling required. Severity classification not done. LUS not used
Messner et al. [78]	5 IPF, 10 healthy subjects	Binary classification (healthy subjects vs patients with IPF)	GRNN	F-score 72.1% Se 71.5%	Small number of patients. Manual crackles labelling required. Severity classification not done. LUS not used
Ono et al. [79]	21 IPN, 10 healthy subjects	IPN detectability and severity classification	FFT	Spectral analysis of lung sounds is useful in the diagnosis and evaluation of the severity of IPN	LUS not used
Pancaldi et al. [17]	70 RA patients (27 ILD + , 43 ILD-)	Identifying RA patients with possible ILD using lung sound-based binary classification (presence vs absence of ILD) compared with chest HRCT	FFT	Acc 90%, Se 92.6%, Sp 88.4%	No healthy subjects. Severity classification not done. LUS not used
Santiago-Fuentes et al. [80]	19 ILD (10 IPF, 9 CPFES)	Binary classification (IPF vs CPFES)	AR model, SNN	Performance evaluation of the neural network: Acc 90.7% to 97.3%, Se 91.8% to 98.3%, Sp 87.5% to 96.3%	No healthy subjects. Severity classification not done. LUS not used
Sen et al. [81]	10 obstructive bronchiectasis, 10 ILD, 20 healthy subjects	Binary (healthy vs pathological) and three class (healthy, bronchiectasis and ILD) classifiers	AR model, SVM	Se 85%, Sp 85% Se 100% (three-class classifier)	Small number of patients. Severity classification not done. LUS not used

ACC, accuracy; AR, autoregressive; AUROC, area under the receiver-operating curve; BPNN, backpropagation neural networks; CHF, congestive heart failure; CF, cystic fibrosis; COPD, chronic obstructive pulmonary disease; CPFES, combined pulmonary fibrosis with emphysema syndrome; CTD, connective tissue diseases; CRNN, convolutional recurrent neural network; FFT, fast Fourier transform; GB, Gaussian Bayes; GRNN, gated recurrent neural network; HRCT, high-resolution computed tomography; ILD, interstitial lung disease; IPF, idiopathic pulmonary fibrosis; IPN, interstitial pneumonia; k-NN, k-nearest neighbor; LUS; lung ultrasound; MPNN, message passing neural network; PN, pneumonia; RA, rheumatoid arthritis; Se, sensitivity; SNN, supervised neural network; SOM, self-organizing map; Sp, specificity; SVM, support vector machine

However, there are some notable differences in these studies, which justify the present work. The main ones are the frequent absence of healthy subjects as a control group and the almost unanimous lack of severity classification or joint use of LUS images. As stated by Charleston-Villalobos et al. [68], a comparison with other attempts to diagnose and classify lung sounds is difficult due to the difference in data acquisition, type of classification scheme, lack of gold standards allowing standardization between studies, and their distinct exploratory nature. In particular, a major flaw of most anterior studies aimed at building deep learning models for diagnostic classification from digital lung sounds is the use of publicly available databases, such as the R.A.L.E repository [82] or the International Conference on Biomedical Health Informatics [83]. These databases have inherent acquisition flaws due to heterogeneity in data collection and methods that create systematic biases between the predicted labels on which new algorithms are built. This is then reflected in the results of studies with an exaggerated excellent predictive performance that prevents their evaluation and comparison with each other. On the contrary, in our study, sounds will come from a cohort of patients under standardised and homogeneous recording conditions. It remains to be determined whether an AI algorithm using respiratory sounds and/or LUS analysis can be used as an initial and accurate diagnostic tool for patients with ILDs or COPD. The diagnosis of IPF, NSIP and COPD in early stages may allow practitioners to appropriately recognise exacerbations of a chronic lung disease, whereas patients may initially be diagnosed as having multiple bouts of acute disease (e.g., bronchitis) without this defined diagnosis [61]. Early diagnosis with AI may therefore allow patients to benefit from prevention measures and the allocation of appropriate treatments aiming to reduce the progression to permanent lung damage and improve the overall prognosis in patients presenting at primary care clinics for non-specific chronic respiratory symptoms. As research in this area is scarce, it is anticipated that the results generated from this study will be of great importance and may be sufficient to change and improve pulmonary primary care practice in a vulnerable population by proposing a faster diagnosis.

This study has several limitations. First, the interpretation and data generated by the algorithm at this stage of our research will not be used for diagnostic purposes or treatment decisions. Both of these points will require further dedicated validation studies in clinical contexts. Second, selection bias can occur in case–control studies when control subjects are not truly representative of the population that produces the cases. In this study, both populations will stem from the same source population in a single-centre outpatient clinic, which may suggest more acute symptoms and pathological lung sounds than those encountered in ambulatory care services. Third, since patients with already-diagnosed IPF, NSIP and COPD will be enrolled, we will not be able to confirm whether *DeepBreath* would have detected these patients at earlier stages. Finally, we acknowledge that the sample size is modest, but it appears to be sufficiently powered in the context of a pilot study.

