## Methods

### Study design

This is a single-centre, prospective, population-based, case–control study that will be carried out in subjects with IPF, NSIP and COPD within a pulmonology outpatient clinic in Switzerland, with a total of approximately 7000 specialised consultations per year. Figure 1 shows the study flowchart and Table 1 details the study schedule. The present study protocol adheres to the Strengthening the Reporting of Observational studies in Epidemiology (STROBE) Statement [41].

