### Population

Inclusion criteria are consecutive, consenting adult outpatients (> 18 years) with IPF (group 1), NSIP (group 2) and COPD (group 3) already diagnosed prior to the consultation (index) date. Probable and definitive IPF diagnosis will be made according to the Fleischner Society Consensus [42], NSIP diagnosis with the American Thoracic Society classification [2, 43], and COPD with the Global Initiative for Chronic Obstructive Lung Disease criteria [44]. Consenting, age-matched (± 2.5 years) individuals with normal lung function (spirometry, lung volume and transfer factor for carbon monoxide [TL_CO_]) followed in the outpatient clinic with a similar quality of electronic medical records, but for diseases other than the outcome of interest, will serve as the 1:1 control group (group 4). This latter group will comprise patients with obstructive sleep apnoea, follow-up of occupational lung diseases (miners, chemical workers, etc.), and follow-up of pulmonary nodules (considered benign after 2 years). Reasons for pulmonary follow-up among the controls will be reviewed and reported in a supplementary file. Identifying all cases with the outcome of interest and selecting controls for comparison is a more efficient and resource-sparing study design than a full cohort study. Exclusion criteria are: (1) patients who cannot be mobilised for posterior auscultation; (2) those known for severe cardiovascular disease with pulmonary repercussions; (3) patients known for a concurrent, acute, infectious pulmonary disease (e.g., pneumonia, bronchitis); (4) patients known for asthma exclusive from COPD; (5) patients with alpha-1-antitrypsin deficit; (6) a physical inability to follow procedures; and 7) inability to give informed consent.

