### Study procedure

The study will be performed over a period of 6 months. Recruitment can be stopped before the anticipated end if the inclusion of 160 patients is reached before. A trained research nurse/doctor ([name]) will recruit the subjects during a single routine consultation in the outpatient clinic. This will include checking the selection criteria for each patient prior to study participation, obtaining written informed consent, administering questionnaires on demographic characteristics (age, sex, occupation, long-term exposure to occupational or environmental agents, etc.), relevant medical history, and symptomatic presentation (Additional file 1), which will be captured by an electronic case report form to be completed by the study coordinator on a tablet. The nurse/doctor will also administer the standardised K-BILD [47], CAT [48], and SF-36 [49] severity assessment questionnaires, and record lung sounds during 5–7 min with an electronic stethoscope in the same zones as LUS acquisition, as previously proposed by our group [40]. For the LUS examination using a standard point-of-care ultrasound device, an adapted version of our previous 10-point acquisition protocol [50] will be used, which involves scanning the anterior superior, anterior inferior, posterior superior, posterior inferior and lateral thorax regions. In addition, pulmonary functional tests (conducted with patients in a stable condition) will be collected, as well as chest X-rays with two incidences (posterior-anterior and lateral) and HRCT scans for IIP patients (within 12 months). Controls will not be exposed to a chest X-ray and/or CT scan unless required as part of their routine follow-up; cases will have undergone such imaging given that it is part of their diagnostic evaluation.

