### Statistical analysis plan

For descriptive statistics related to the clinical data collected, all continuous variables will be reported as medians with their interquartile ranges. Binary and categorical variables distribution will be reported as proportions and percentages. To evaluate baseline demographic differences and outcomes differences between the case and control patients, conditional logistic regressions will be used to account for the matched design. Pearson’s and Spearman’s correlation coefficients will be used to assess the relationship between continuous variables normally and non-normally distributed, respectively. For the primary outcome, each task will be quantified using descriptive statistics (i.e., proportion and type of abnormalities), as well as the AUROC, sensitivity, specificity, positive predictive value, negative predictive value, and likelihood ratios (with 95% CIs over a fivefold cross-validation).

The diagnostic accuracy of each echographic sign will be assessed and sensitivity, specificity, positive predictive value, negative predictive value, positive likelihood ratio, and negative likelihood ratio with their 95% CIs will be calculated. To find the combination of echographic signs with the best diagnostic accuracy, we will compare the performance of several multivariable models, such as logistic regression, random forest and neural networks. Performance will be reported on a test set comprising 20% of the data in a tenfold cross-validation with 95% CIs. As a secondary objective, we will aim to compare the predictive performance of human expert-identified acoustic signatures in the above predictive tasks. First, we will describe the expert labels by the percentage of sound labels attributed to each diagnosis. A multivariable logistic regression will be derived using the clinical data and sound labels to estimate the diagnoses, as for the primary objective. A kappa score will be used to assess the concordance between *DeepBreath* and expert diagnosis consolidated into a basic predictive model.

The K-BILD, CAT and SF-36 questionnaires will be analysed with descriptive statistics. Associations between the questionnaires’ sum scores and lung function parameters will be quantified by Spearman’s rank correlation coefficient. We will consider correlations < 0.3 as negligible, ≥ 0.3 to < 0.5 as low, ≥ 0.5 to 0.7 as moderate, and ≥ 0.7 as strong.

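### Controls share the clinic with cases but some attend because of an occupational exposure, so exposure comparisons and ILD-versus-control models that use clinical data can reflect how controls were recruited

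*Protocol article*

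**What the plan says.** The Study design section calls this a "single-centre, prospective, population-based, case–control study". The limitations in the Discussion name selection bias, in the sense of controls who do not represent the population that gave rise to the cases, and reply that "In this study, both populations will stem from the same source population in a single-centre outpatient clinic".

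The Population section describes the controls as "age-matched (± 2.5 years) individuals with normal lung function" who are followed in the clinic for other conditions. It continues: "This latter group will comprise patients with obstructive sleep apnoea, follow-up of occupational lung diseases (miners, chemical workers, etc.), and follow-up of pulmonary nodules". Age is the only stated matching variable. No number or ceiling is set for any of the three groups. The reasons for follow-up are to be reviewed and listed in a supplementary file.

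Occupation and long-term occupational exposure are collected. The Study procedure section refers to "questionnaires on demographic characteristics (age, sex, occupation, long-term exposure to occupational or environmental agents, etc", and the Questionnaires section also places such exposure under demographics.

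The Statistical analysis plan section states: "To evaluate baseline demographic differences and outcomes differences between the case and control patients, conditional logistic regressions will be used". Secondary outcome 3 explores adding clinical data, with demographics and medical history among them, to the breath-sound algorithms. The section on synergy with clinical data repeats this, and the Statistical analysis plan section puts clinical data into a multivariable logistic regression for diagnosis.

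**The concern.** A control group should show how common an exposure is in the population that produced the cases. Patients under follow-up for occupational lung disease cannot do that for occupational exposure, because exposure is why they attend. The larger their share of the control group, the more exposed the controls look, whatever the relation between exposure and ILD.

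Two outputs are at stake. The first is any case-control comparison of occupation or occupational exposure made under the baseline demographic analysis. The second is the set of ILD-versus-control models that use clinical data. There, exposure, or a history entry recording the occupational disease, can act as a label for control status. The gain credited to clinical data would then partly reflect recruitment and would not carry over to another setting.

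The design does not correct this. Age matching and conditional regression deal with age. Listing reasons for follow-up discloses the problem without removing it.

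**Working it through.** The plan gives no exposure prevalence, exposure odds ratio or occupational share, so it has no figure to reproduce. The check shows direction and plausible size under stated assumptions.

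**Inputs**
- 80 ILD and 40 controls (Sample size calculation section); two-sided 5% tests (end of the statistical section).
- Assumed: exposure prevalence p0 in the true source population; prevalence p1 in ILD; share f of controls from occupational follow-up, all counted as exposed.
- Unmatched approximation.

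**Formulas**
- Exposure among controls: q = f + (1 − f)·p0.
- Observed odds ratio: OR = [p1/(1 − p1)] / [q/(1 − q)].
- The observed OR equals 1 when f = (p1 − p0)/(1 − p0).
- Chance of a significant difference ≈ Φ[(|q − p1| − 1.96·SE0)/SE1], where SE0 uses the pooled proportion and SE1 the separate ones.
- AUROC of exposure alone, with unexposed read as ILD: [(1 − p1) + q]/2.

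**No true association, p0 = p1 = 20% (true OR 1)**

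| f | q | Observed OR | Chance of a false significant difference | AUROC of exposure alone |
|---|---|---|---|---|
| 10% | 0.28 | 0.25/0.389 = 0.64 | 17% | (0.80 + 0.28)/2 = 0.54 |
| 20% | 0.36 | 0.25/0.5625 = 0.44 | 48% | (0.80 + 0.36)/2 = 0.58 |
| 1/3 | 0.467 | 0.25/0.875 = 0.29 | 85% | (0.80 + 0.467)/2 = 0.63 |

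At f = 1/3 the expected counts are 16 exposed and 64 unexposed ILD patients, and 18.67 and 21.33 controls. The standard error of the log OR is √(1/16 + 1/64 + 1/18.67 + 1/21.33) = 0.423, which gives a 95% interval of 0.12 to 0.65. With p0 = p1 at 10% and at 30%, the OR at f = 1/3 is 0.17 and 0.38.

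The last column shows how a classifier could gain from exposure with no disease information in it. It refers to exposure alone. The increment over lung sounds cannot be derived from the documents.

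**If a true positive association existed**
- p0 = 20%, p1 = 35% (true OR 2.15): observed OR 1.38, 0.96, 0.62 and 0.36 at f = 10%, 20%, 1/3 and 50%. The crossing point is 0.15/0.80 = 18.75%, or 7.5 of 40 controls.
- The same, with only 90% of occupational controls counted as exposed: 1.46, 1.05 and 0.70 at f = 10%, 20% and 1/3.
- p0 = 20%, p1 = 50% (true OR 4.0): observed OR 1.14 at f = 1/3. The crossing point is 0.30/0.80 = 37.5%.
- Over the six prevalence pairs tried, the crossing point ran from 11% to 37.5%.

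The shift is downward in every case. Whether it passes 1 depends on values the documents do not give.

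**After the fix.** With f = 0, q = p0 and the observed OR equals the true one. Removing a one-third share leaves 40 × 2/3 ≈ 26.7 controls, of whom 5.33 are exposed and 21.33 unexposed under no association. The standard error becomes √(1/16 + 1/64 + 1/5.33 + 1/21.33) = 0.559, and the interval around 1 is 0.33 to 2.99.

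**The case against.** The strongest reply is that the protocol plans no study of causes. Its objectives are diagnostic classification, severity, crackle associations and quality of life. Occupational exposure enters the case-control comparison only when the demographic lists are read together with the analysis section. A table showing more exposed workers among controls would correctly describe who was enrolled. This stands: the odds ratio misleads only if it is read beyond the sample, and so labelling it as description is an acceptable remedy.

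A reader might infer that the plan will make a real occupational cause of ILD look protective. The documents do not support that. The Background lists occupational factors among known causes of ILD in general, but places IPF and NSIP, the ILDs enrolled here, within the idiopathic group. The true odds ratios above 1 used in the working are therefore illustrations without a basis in the text, and a strong association would only be weakened. The no-association case needs no such premise.

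The sentence in the limitations is literally true of the clinic, and it goes on to concede that the patients may be more symptomatic than those in ambulatory care. That caveat concerns disease spectrum. It does not address exposure among controls.

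Finally, the work with clinical data is partly exploratory, and no section names occupation as a model input. That makes the effect on the models conditional. Secondary outcome 3 does, however, count demographics and medical history as clinical data, and the protocol files occupational exposure under demographics.

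**Conclusion.** The point holds in limited form. The same-source statement and the population-based label do not fit a control group selected by reason for follow-up, one of those reasons being an exposure-related disease. Comparisons of occupational exposure are shifted towards controls by an amount set by an uncapped share. With an assumed 20% exposure, a one-third share and no true association, the odds ratio is about 0.29 (95% interval 0.12 to 0.65, unmatched approximation). At a 10% share it is 0.64. Reversal of a true positive association is possible but not certain.

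ILD-versus-control models with clinical data can absorb the same artefact and overstate the value of adding those data. It would be tempting to extend this to the primary diagnostic results, but models on audio alone or ultrasound alone do not take exposure as an input, and nothing here shows that they are affected.

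**What to change.** - **Study design and limitations:** drop the population-based label, and replace the same-source statement with one saying that controls attend the same clinic but are selected by diagnosis.
- **Statistical analysis plan section:** leave occupational-follow-up controls out of any comparison of occupation or occupational exposure, or present that comparison explicitly as a description of the sample.
- **ILD-versus-control models with clinical data:** leave out occupation and occupational exposure (and any history item recording the occupational disease), or refit without occupational-follow-up controls and report both results.

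Reasons for follow-up among controls are already to be reviewed, so no new data are needed. The cost is some rewording, one restricted analysis, fewer controls and a wider interval. In the example above, the standard error of the log odds ratio rises from 0.423 to 0.559.
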